### Data analysis

*Questionnaire validation*

The kappa coefficient (k) and content validity index (CVI) will be used to quantify the degree of agreement among experts during content validation. In order to assess the reliability of the instrument, the test and retest results will be evaluated using the intra-examiner agreement test (kappa test,
*k*), which is the appropriate statistical procedure to assess the reliability of categorical and nominal variables. The criterion validity will be analyzed by comparing the results of the teleconsultation with those of the face-to-face consultation using the chi-square test (χ
^2^). The significance level will be set at 5%, and the data will be analyzed using
Jamovi and
RStudio software.

*Randomized clinical trial*

Primary outcome: pain (Wong-Baker scale); secondary outcomes: quality of life (questionnaires according to age group) and missing teeth.

The primary outcome of the randomized clinical study will be any change in pain score observed at the 7-day and 14-day follow-up timepoints compared to baseline. This outcome comprises an ordinal qualitative variable; therefore, comparison between the teleconsultation and face-to-face consultation groups will be performed using the Mann-Whitney test.

Other secondary outcomes will be evaluated, such as the impact of treatments on oral health-related quality of life, and the number of missing teeth after the 24-month follow-up period. Differences between the groups regarding the final and initial scores of the questionnaires on oral health-related quality of life, as well as the number of missing teeth, will be compared using Student’s t test or the Mann-Whitney test, depending on the type of data distribution (normal or non-normal). In addition, Poisson’s regression analysis will be performed to assess the influence of other variables on the results. The significance level will be set at 5%, and the data will be analyzed using Jamovi and RStudio software.

*Before-after study nested within an RCT*

Descriptive analyses regarding diagnosis for needing urgent treatment will be performed using the teletriage questionnaire, alone and in combination with the face-to-face consultation. The possible treatment decision outcomes for these analyses, and for both the remote and the face-to-face examination, will be (i) the need for urgent treatment or (ii) the possibility of elective treatment. The frequency of change in the treatment decision will be calculated considering that the change can be (i) from urgent to elective treatment or (ii) from elective to urgent treatment. Explanatory variables related to the children, such as sex, age (randomization strata), and caries experience may be used in the analyses. The primary outcome in this study will be any change in treatment decision after the face-to-face consultation. Prevalence ratio (PR) values and respective 95% confidence intervals (95% CI) will be calculated, and univariate and multiple regression analyses will be performed. The significance level will be set at 5%, and the data will be analyzed using Jamovi and RStudio software.

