### Assignment

*Questionnaire validation*

The questionnaire will be applied to 140 participants, and reapplied to 14 randomized participants. Randomization, in blocks of four participants, will be performed using statistical software (MedCalc
^®^ 15.11, MedCalc Software, Ostend, Belgium), and the sequence generated will be distributed in sealed brown envelopes.

*Before-and-after study nested within a randomized clinical trial*

Randomization, in blocks of four patients, to assign them to one of the treatment groups, will be performed using statistical software (MedCalc
^®^ 15.11, MedCalc Software, Ostend, Belgium), and the sequence generated will be distributed in sealed brown envelopes. The envelopes must be opened immediately after the start of the teleconsultation.

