### Training of examiners/researchers

The examiners/researchers (authors on the paper and two dental practitioners based at the clinics) will be trained by the author responsible for the project ([name]) to carry out the research prior to the first stage. This will involve a four hour training program for urgency situations of dental origin in children, and a 4-hour calibration program for questionnaire application.

Prior to the beginning of the study, the researcher will explain the study and how teledentistry will be used within the Family Health Units to the entire team.

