### Sample size

*Sample for questionnaire validation*

The guidelines of the European Statistical System stipulate that the development and validation of instruments must follow five steps: (1) conceptualization, (2) questionnaire design, (3) questionnaire testing, (4) revision, and (5) data collection.
^
34
^ Considering that the questionnaire conceptualization and design have already been completed, our considerations will begin from the questionnaire testing step. The first step involved in instrument testing is evaluation by a panel of experts (content validation). There is a controversy in the literature regarding the recommended size for this panel, ranging from five to twenty members,
^
35
^
^,^
^
36
^ depending on their experience and qualifications. Subsequently, data collection will be carried out by applying the questionnaire (criterion validity). To this end, a sample size of at least 10 participants is recommended for each item
^
37
^; therefore, the minimum sample size of the present study will be 140 subjects. In order for the instrument to be considered reliable (test and retest), it must be able to produce similar results when applied to the same individual at different times, and by different interviewers. For this purpose, a sample size corresponding to 10% of the total “N” (i.e., 14 patients in the current version of the questionnaire) should be used.

*Sample size calculation for the RCT*

Primary outcome: the presence of dental pain in children and adolescents, considering independent samples (in this case, there is no pairing of individuals, and the interventions will be assigned to different individuals). The possibility of dropouts during the follow-up period was taken into account.

In performing the sample size calculation for independent samples, the proportion of dental pain observed in children and adolescents will be considered as 32.7%,
^
38
^ and the minimum, clinically relevant proportion difference will be 15%. Thus, considering a two-tailed test, a significance level of 0.05, and a power of 0.80, the calculation will yield a total number of 236 patients. Owing to the possibility of participant dropout during the follow-up period, 10% of this number will be added to the final sample, bringing the total number of patients required per experimental group to 130 (G Power, version 3.1.9.4).

*Sample size calculation for the before-and-after study*

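### The questionnaire must be reliable over time and across interviewers, but the retests are analysed as intra-examiner agreement only, so the between-interviewer component is not assessed

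*Protocol article*

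**What the plan says.** The protocol article sets the reliability criterion under Sample size (Sample for questionnaire validation). To count as reliable, "it must be able to produce similar results when applied to the same individual at different times, and by different interviewers". It then ties the retest sample to that criterion: "a sample size corresponding to 10% of the total “N” (i.e., 14 patients in the current version of the questionnaire) should be used".

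The Assignment section gives the procedure: "The questionnaire will be applied to 140 participants, and reapplied to 14 randomized participants". Research design repeats this. Neither section says who conducts the second application.

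Data analysis (Questionnaire validation) fixes the reliability statistic: "the test and retest results will be evaluated using the intra-examiner agreement test", with kappa as the measure. The only other kappa in the validation stage "will be used to quantify the degree of agreement among experts during content validation". Criterion validity is a chi-square comparison of the teleconsultation with the face-to-face consultation.

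On staffing, "The examiners/researchers (authors on the paper and two dental practitioners based at the clinics) will be trained", and that training includes a four-hour calibration in applying the questionnaire.

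**The concern.** Intra-examiner agreement holds the examiner constant. It shows whether one person gets the same answer twice. It cannot show whether two people get the same answer, because variation between them is excluded by design. The criterion under Sample size names both properties and the analysis covers one.

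The missing half matters for the use the authors have in mind. Objective 3 is a reception and risk-classification protocol for an urgency service, and the study hypothesis rests on a validated questionnaire. A tool for such a service should give similar classifications in different hands. A same-examiner retest is also open to that examiner's memory of the first answers. If the result were then reported as meeting the stated criterion, the validation claim would go further than its evidence.

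**Working it through.** **1. The plan's own figure.** Ten participants per item and 140 participants imply 140 / 10 = 14 items. The retest sample is 0.10 × 140 = 14. Both agree with the text, so the retest arithmetic is not in question.

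**2. Requirement against analysis.**

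| Planned element | What it compares | Over time? | Between interviewers? |
|---|---|---|---|
| Intra-examiner kappa on 14 retests | Same examiner, two occasions | Yes | No |
| Expert kappa and content validity index | Experts judging content | No | No |
| Chi-square, remote v. face-to-face | Two methods of consultation | No | No |
| Four-hour calibration | No agreement statistic stated | No | No |

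No row supplies the between-interviewer component.

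**3. Can one kappa stand in for the other?** The document gives no interviewer variance, so this is an illustration under assumptions. Let latent urgency have variance 1, occasion error SD 0.4 (variance 0.16) and the interviewer effect variance v, drawn afresh for each participant and shared by both applications when the interviewer is the same. With the cut at the median, κ = (2/π) arcsin ρ, where

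- same interviewer: ρ = (1 + v) / (1 + v + 0.16)
- different interviewers: ρ = 1 / (1 + v + 0.16)

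| v | Intra-examiner κ | Between-interviewer κ |
|---|---|---|
| 0 | 0.66 | 0.66 |
| 0.25 | 0.69 | 0.50 |
| 0.5 | 0.72 | 0.41 |
| 1.0 | 0.75 | 0.31 |

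A simulation of the same model gives the same values. As interviewers differ more, the intra-examiner figure rises slightly while the between-interviewer figure falls. A good value of the first is therefore no evidence about the second.

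**4. Precision with 14 retests.** Assume a binary rating, equal marginals, true κ of 0.6 to 0.8 and an urgent prevalence p of 0.5 to 0.8 (none of these is in the document), and use the large-sample Fleiss-Cohen-Everitt standard error.

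- Narrow end, κ = 0.8 and p = 0.5: observed agreement 0.90, chance agreement 0.50. SE = √[0.90 × 0.10 / (14 × 0.50²)] = 0.160; half-width 1.96 × 0.160 = 0.31.
- Wide end, κ = 0.6 and p = 0.8: cells 0.736, 0.064, 0.064, 0.136; chance agreement 0.68. The variance numerator is 0.1914 + 0.0205 − 0.1076 = 0.1042. SE = √[0.1042 / (14 × 0.32²)] = 0.270; half-width 0.53.

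Splitting the retests into two sets of 7 multiplies these by √2, giving about 0.44 to 0.75, which is uninformative. With 140 pairs the half-width would be about 0.10 to 0.17.

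**The case against.** The best defence is that the retest interviewer is never named. The only text describing the conditions of repetition is under Sample size, and it speaks of different interviewers; the word intra-examiner may be a loose label for test-retest kappa. Who makes the second call is also the sort of detail that a condensed article leaves to the full protocol. This is fair, and it rules out any claim that the same examiner will certainly repeat the interview. It does not remove the conflict: the article fixes a named form of agreement that does not match its own criterion, and that name determines how the reported kappa will be read.

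Three stronger readings are tempting and are not supported:

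- *Reliability is not measured at all.* A retest by the same examiner does measure consistency over time, which is one of the two stated components.
- *The randomised trial is undermined.* Research design has each trial teleconsultation done by one trained researcher; the two blinded researchers perform the face-to-face examination with a dental record. The trial's primary outcome is pain, which does not depend directly on interviewer kappa.
- *The error can be put at a definite number of wrong triage decisions.* Discordance equals (1 − κ) × 2p(1 − p). With p = 0.8, κ = 0.9 gives 3.2% and κ = 0.7 gives 9.6%, but this only restates chosen inputs. In 14 retests it is 14 × 0.032 ≈ 0.4 against 14 × 0.096 ≈ 1.3 discordant cases, which so small a sample cannot tell apart.

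**Conclusion.** The inconsistency stands in limited form. Followed literally, the analysis covers repeatability over time and leaves agreement between interviewers unassessed, although the 14 retests were assigned to both. The internal mismatch rests on the text alone. Its numerical size is unknown: the kappa contrast depends on assumed interviewer variances, and the interval widths on assumed kappas and prevalences. The effect is confined to what may be claimed for the validated questionnaire. It deserves correction because the criterion is the authors' own and meeting it costs little.

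**What to change.** Choose one of two courses and make the two sections agree.

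1. *Keep the criterion.* State that the 14 retests are done at a later time by a different calibrated interviewer who has not seen the first result. In Data analysis, replace the intra-examiner label with inter-examiner test-retest kappa, reported with a 95% CI.
2. *Narrow the claim.* Delete the between-interviewer clause from Sample size and limit the reliability statement to same-examiner repeatability. This is also the course if the retests have already been done by the same examiner.

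Do not divide the 14 retests between the two set-ups.

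The first course costs a sentence and a scheduling rule. Several people are already being trained and calibrated, and Study status places the questionnaire still in validation. It has drawbacks that should be stated. One kappa then combines time and interviewer effects, so low agreement could not be attributed to either. A new interviewer does not remove the parent's own recall of the first answers. With 14 pairs the interval stays wide, so the result should be reported as an estimate with its uncertainty.

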### Objectives

The foremost aim of this study will be to analyze the effectiveness of teletriage and of an urgency/emergency risk classification system for children, compared to face-to-face consultation for these patients. Secondarily, other key issues will be investigated, as follows:
1 -validation of a questionnaire for dental urgency screening in children;2 -assessment of the level of agreement among diagnoses and risk ratings assigned to cases screened in person versus remotely;3 -proposal and testing of an oral health protocol for patient reception and risk classification for children seeking an urgency/emergency dental care service.

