### Inclusion and exclusion criteria

The inclusion criteria will be the same for the two stages of patient selection in the study.

*Inclusion criteria*
a)children aged 3 to 13 years, with dental pain, whose parents seek urgent care at the Dental School of the University of São Paulo in São Paulo, or at the public network in the city of Carangola, in the state of Minas Gerais.b)patients with a sufficiently good internet connection to allow a synchronous consultation.

*Exclusion criteria*

The exclusion criteria will be the same for the two stages of patient selection of the study:
a)patients who fail to attend the face-to-face consultation, when assigned to G2;b)patients with internet access difficulties.

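### Criterion validity of the teletriage questionnaire rests on a chi-square test, which shows association in either direction but not agreement or accuracy

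*Protocol article*

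**What the plan says.** All references are to the protocol article.

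- **Data analysis, Questionnaire validation.** Content validity uses kappa and a content validity index among experts, and test-retest reliability uses kappa. Criterion validity is assessed by "comparing the results of the teleconsultation with those of the face-to-face consultation using the chi-square test". The section closes with "The significance level will be set at 5%, and the data will be analyzed using" two named packages. No other analysis of remote against in-person results is named for this stage.
- **Objectives.** The second secondary objective is "assessment of the level of agreement among diagnoses and risk ratings assigned to cases screened in person versus remotely".
- **Data analysis, Before-after study nested within an RCT.** Each G2 child has a remote and an in-person decision, urgent or elective. "The frequency of change in the treatment decision will be calculated", separately for the two directions, and the primary outcome of this part is a change in either direction. Prevalence ratios with 95% CIs and regressions on child characteristics are added.
- **Sample size.** "the minimum sample size of the present study will be 140 subjects" for validation. The before-and-after study has 130 children.
- **Inclusion and exclusion criteria.** Both stages admit "children aged 3 to 13 years, with dental pain".

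**The concern.** A triage tool is useful if it reaches the same decision as the clinician and, above all, if it does not send away children who need urgent care. Chi-square measures neither. Its null hypothesis is that the two results are unrelated. Rejecting it shows only that the questionnaire carries some information, and the statistic is the same whether the results tend to coincide or to oppose each other.

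The protocol uses kappa where experts or repeat applications are compared, but not where remote and in-person results are compared, although the second secondary objective asks for exactly that agreement. The change frequency in the nested study covers part of the objective: raw agreement on the binary urgency decision. Diagnoses and risk ratings have no named agreement analysis.

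The Abstract places validation before the 260-child trial, and the hypothesis in the Conclusions is framed around a validated questionnaire. The evidence behind that word should therefore answer the right question.

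**Working it through.** **The plan's own figures.** The Sample size section gives the rule "a sample size of at least 10 participants is recommended for each item" and arrives at 140, which implies 140/10 = 14 items; the item count itself is not stated. The retest sample is "a sample size corresponding to 10% of the total": 0.10 × 140 = 14, as stated. No accuracy, kappa or urgency prevalence is given, so the tables below are illustrations under stated assumptions.

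**Notation.** a = urgent by both; b = remote urgent, in-person elective; c = remote elective, in-person urgent; d = elective by both; n = a+b+c+d.
- Chi-square = n(ad − bc)² / [(a+b)(c+d)(a+c)(b+d)], uncorrected.
- Sensitivity = a/(a+c); specificity = d/(b+d).
- Kappa = (po − pe)/(1 − pe), with po = (a+d)/n and pe = [(a+b)(a+c) + (c+d)(b+d)]/n².

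**Step 1. How little is needed for significance at n=140.** The smallest significant phi is 1.96/√140 = 0.166. With half the children urgent and sensitivity equal to specificity, this is 0.5 + 0.166/2 = 0.583, hardly better than a coin toss.

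**Step 2. Weak tool, 60% urgent (assumed): a/b/c/d = 50/20/34/36.**
- Chi-square = 140 × (1800 − 680)² / (70 × 70 × 84 × 56) = 7.62, p=0.006.
- Sensitivity 50/84 = 60%, so 34 of 84 urgencies (40%) are missed. Specificity 36/56 = 64%.
- po = 86/140 = 0.614, pe = 0.5, kappa = 0.23.

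A second case, 70% urgent, 49/7/49/35: sensitivity 49/98 = 50%, kappa 0.26, chi-square 13.61, p=0.0002.

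**Step 3. Inverse tool, 50% urgent (assumed): 14/56/56/14.** Chi-square = 140 × (196 − 3136)² / 70⁴ = 50.4, p<0.001. Here po = 0.2, pe = 0.5 and kappa = -0.60.

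**Step 4. About the same accuracy, other case mixes, n=140.**
- 90% urgent, 76/5/50/9: sensitivity 76/126 = 60%, specificity 9/14 = 64%, chi-square 3.13, p=0.077.
- 95% urgent, 80/2/53/5: sensitivity 80/133 = 60%, specificity 5/7 = 71%, chi-square 2.73, p=0.098.

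With sensitivity held at about 60%, p moves from 0.006 to 0.098 as the share of urgent cases changes. The p-value does not track accuracy.

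**Step 5. Change frequency at n=130.** The change rate is (b+c)/n = 1 − po, the complement of raw agreement.
- 58/6/7/59: change 13/130 = 10%, pe = 0.5, kappa = 0.80. Missed urgencies 7/65 = 11%; over-triage 6/65 = 9%.
- 117/13/0/0 (every child called urgent): change 13/130 = 10%, pe = 0.9, kappa = 0. Missed urgencies 0/117; over-triage 13/13 = 100%.

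One change rate covers a good tool and one that does not discriminate at all. The denominators of the in-person decision separate them.

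**Step 6. Is estimation feasible with the planned 140?** Normal-approximation 95% half-widths, 1.96 × √[p(1−p)/m], at an assumed value of 0.85:
- Sensitivity: ±0.084 with m=70 (50% urgent); ±0.066 with m=112 (80% urgent).
- Specificity: ±0.132 with m=28 (80% urgent). With only 7 elective children, 5/7 has an exact 95% CI of 29% to 96%.
- Kappa 0.80 with balanced margins: about ±0.10.

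**The case against.** The strongest reply has several parts, and much of it stands.

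- **The change frequency does measure agreement.** On a paired binary decision it is one minus raw agreement, and the plan splits it into the over-triage and under-triage directions. It would be wrong to say that no agreement measure is planned. What is missing is chance correction, conditioning on the in-person decision, and any coverage of diagnosis and risk rating.
- **A low change rate is not assured by the case mix.** A reader might infer this because every entrant has pain and the non-urgent list under Interventions is largely routine or asymptomatic care. Urgency prevalence is not stated, and in both tables of Step 4 the change rate is 55/140 = 39% with 90% to 95% urgent. It is low only if teletriage also calls nearly everyone urgent.
- **In a very urgent-heavy sample chi-square would not pass the weak tool.** Step 4 confirms this. The examples in Step 2 depend on 60% to 70% being urgent.
- **Chi-square does not mishandle pairing.** Each child contributes one cell, and independence of the two classifications is the null hypothesis, not a violated assumption.
- **The protocol states no rule that p<0.05 means valid.** A reader might infer one, since no other criterion-validity analysis is named, but it is not written. An acceptance threshold may sit in a full protocol or SAP that is not shown, so its absence is not the complaint.

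None of this rescues chi-square as the stated criterion-validity analysis. Nor is the matter merely deferred: the article names the method, and the method answers a different question.

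**Conclusion.** The concern holds in a limited form. The criterion-validity analysis is wrong as written: at 140 children it can be significant for a questionnaire that misses 40% of urgencies (p=0.006, kappa 0.23, 60% urgent assumed) and for one that is systematically inverted (p<0.001, kappa -0.60, 50% urgent assumed). A significant result would not support a claim of validity, and a non-significant one would not measure how poor the tool is.

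The objective on agreement is only partly served. Raw agreement on urgency can be obtained from the planned change frequency; chance-corrected agreement, and any agreement on diagnosis or risk rating, is not named. The figures rest on a binary remote and in-person result, uncorrected chi-square, and assumed prevalence and accuracy. The analysis of pain, the RCT's primary outcome, is not affected.

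**What to change.** **Data analysis, Questionnaire validation.** Replace chi-square as the criterion-validity analysis. Report the paired 2×2 table with sensitivity, specificity and predictive values against the in-person decision (exact 95% CIs), and kappa with its CI. Base the claim of validity on the lower confidence limit for sensitivity, against a value fixed before the data are analysed.

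**Data analysis, Before-after study.** Keep the change frequency, and also report each direction on its in-person denominator: missed urgencies among children judged urgent in person, and over-triage among those judged elective. Add kappa for the urgency decision and for diagnosis, and weighted kappa for the risk rating, so that the second secondary objective has an analysis.

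**If few elective cases enrol,** limit the validity claim to sensitivity. Eligibility should not be widened to children without pain to gain specificity, because that changes the population defined under Inclusion and exclusion criteria.

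**Cost.** Analysis wording only: no extra children, no extra visits. Study status says the questionnaire is still being validated, so the change can be made before analysis. The drawback is that specificity may be imprecise, and the report should say so.

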**Figure 3. f3:**
[figure not shown]
Inclusion of patients in the randomized control trial (before and after). G1, teleconsultation; G2, teleconsultation plus face-to-face consultation.

Patients in G1 and G2 will be followed up for seven and 14 days using specific instruments to assess the absence or presence of pain (Wong-Baker scale)
^
31
^ and quality of life, according to the child’s age (Child Perceptions Questionnaire, CPQ,
^
32
^ or Early Childhood Oral Health Impact Scale, ECOHIS).
^
33
^ In the case of urgencies involving teeth, a 12- and 24-month follow-up of the tooth reported in the teletriage will be carried out. The clinical criteria used to determine treatment success will be no fistula or exudate, no abscess, no painful symptoms, and no pathological mobility (
Figure 4).

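### The primary Mann-Whitney test ranks unadjusted change in an ordinal pain score; it is valid but inefficient and hard to interpret, and follow-up pain adjusted for baseline should replace it

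*Protocol article*

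**What the plan says.** Under Data analysis (Randomized clinical trial), the primary outcome is "any change in pain score observed at the 7-day and 14-day follow-up timepoints compared to baseline". The section goes on: "This outcome comprises an ordinal qualitative variable", and so "comparison between the teleconsultation and face-to-face consultation groups will be performed using the Mann-Whitney test". Poisson regression is mentioned for the influence of other variables, but nothing adjusts the primary test for baseline pain.

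Other sections bear on this:

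- Inclusion and exclusion criteria: the participants are "children aged 3 to 13 years, with dental pain, whose parents seek urgent care", so every child enters in pain.
- Sample size: "Primary outcome: the presence of dental pain in children and adolescents, considering independent samples". For that calculation "the proportion of dental pain observed in children and adolescents will be considered as 32.7" per cent, with a minimum relevant difference of 15%. The Outcomes paragraph repeats presence of pain as the primary outcome.
- Research design: the 7- and 14-day follow-up uses "specific instruments to assess the absence or presence of pain (Wong-Baker scale").

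**The concern.** The protocol chooses a rank test because the scale is ordinal. But subtracting baseline first treats a step of two faces as the same amount of relief anywhere on the scale, and an ordinal scale does not provide that. The scale is also bounded. A child who reaches 0 can improve by no more than the baseline score, so the ranks of pain-free children carry their entry pain and nothing about the consultation.

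Two things are at stake. A result in which some cured children count as worse than some uncured ones is hard to explain. And a real difference in residual pain may be missed. The second matters more because the protocol calls the trial a noninferiority study: a non-significant result from a weak difference test is easily misread as showing that teleconsultation is no worse. The problem remains once a single follow-up timepoint is chosen, because it lies in the subtraction.

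**Working it through.** **Inputs from the protocol.** 130 per arm; 32.7% with pain; 15-point difference; two-sided 5%; power 80%; all children in pain at entry.

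**Assumed, because the protocol does not give them.** Baseline scores of 2, 4, 6, 8 or 10 in several distributions; the pattern of residual pain; the shape of the effect; 32.7% read as the follow-up rate in one arm; and the direction of the difference.

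**1. The plan's own figure.** For 32.7% v 17.7% (mean 25.2%), the pooled two-proportion formula gives

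n = [1.960·√(2 × 0.252 × 0.748) + 0.842·√(0.327 × 0.673 + 0.177 × 0.823)]² / 0.15² = (1.203 + 0.509)² / 0.0225 ≈ 130.3,

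so 131 per arm and 262 in total. The stated 236 is not reproduced; that is a separate matter and does not decide this point. The dropout step does reproduce: 236 × 1.10 = 259.6, or 130 per arm. By the same formula, power at 130 per arm is Φ[(0.15·√130 − 1.203)/0.605] = Φ(0.84) ≈ 80%. That is the benchmark for a test on presence of pain at follow-up.

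**2. Ranking.** Change = follow-up − baseline.

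- 2 to 0: change −2, pain-free.
- 10 to 6: change −4, still in pain, yet ranked as the better result.
- Any pain-free child: change = 0 − baseline, so the order among these children is baseline reversed.

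In simulated pairs of one cured and one uncured child, with residual pain below baseline, the cured child ranked worse in 1-19% of pairs and tied in 6-17%. This did not occur when residual pain equalled baseline.

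**3. Validity.** With equal arms, rejection rates were 4-6%.

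**4. Power when the arms differ in the share pain-free** (two-sided 5%, Mann-Whitney; adjusted = rank ANCOVA on baseline; a dash means no figure available):

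| Residual pain, assumed | Per arm | Change | Follow-up | Follow-up, adjusted |
|---|---|---|---|---|
| 32.7% v 17.7%, about half of baseline or 2-6, five baseline shapes | 130 | 21-54% | 78-80% | 78-80% |
| Same rates, pain stays at baseline level | 130 | 55-60% | 77-79% | – |
| Same rates, pain stays at baseline level and its risk rises in proportion to baseline | 130 | 70-76% | 78-79% | 81-83% |
| 32.7% v 17.7%, 12 other scenarios | 118 | 17-56% | 73-76% | – |
| 32.7% v 47.7%, same 12 scenarios | 118 | 17-57% | 60-64% | – |
| 32.7% v 5%, or v 60% | 130 | 45-88% | 99-100% | – |

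Baselines concentrated at 8, or at 8-10, gave 60-68% on change against 79-82% on follow-up.

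**5. Power when the effect is graded.** 130 per arm, 1,500 trials; an average drop plus noise (SD 2.5), with one arm improving by 1 extra point:

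| Baseline, average drop | Pain-free | Change | Follow-up, unadjusted |
|---|---|---|---|
| Uniform, 2 | 23-31% | 79% | 48% |
| Uniform, 4 | 40-50% | 61% | 44% |
| Severe, 4 | 22-31% | 79% | 60% |
| Severe, 6 | 41-53% | 61% | 58% |
| Uniform, 6 | 59-69% | 34% | 40% |

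Here change beats the unadjusted follow-up score in four of the five rows. With rank adjustment for baseline, graded runs gave, for example, 82% on adjusted follow-up against 80% on change, 75% against 60%, and 84% against 41%. Adjusted follow-up matched or beat change in every scenario tried under either model.

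**The case against.** The strongest objection is that the large power losses come from a model in which the arms differ only in the chance of reaching exactly 0, which is the least favourable case for change scores. If relief is graded, change often beats the plain follow-up score. This stands. It rules out swapping change for an unadjusted follow-up comparison. It does not rescue change, because adjusted follow-up did at least as well under both models.

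A reader might infer that the protocol itself plans for two thirds of children to be pain-free, since 100 − 32.7 = 67.3%. The Sample size section gives no timepoint, arm or treated population for that figure, and its wording may describe a general prevalence. Reading it as residual pain is an assumption.

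A reader might also infer that the test would miss most real differences, or that it mainly ranks baseline pain. The documents give neither the baseline spread nor the residual-pain pattern needed for such a claim. Several scenarios exceed 50% power at the planned difference, and larger differences are often detected.

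Finally, the quality-of-life scores are also compared as differences from baseline, but no power was worked out for them, so no loss is claimed there.

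**Conclusion.** The point holds as one of efficiency and interpretability. The rank inversion is arithmetic and rests on no assumption beyond the stated outcome and test. There is no bias and no inflation of type I error: randomisation balances baseline on average.

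The size of the power loss is conditional. If the planning figures describe residual pain and the arms differ in the share pain-free, power at 130 per arm is roughly 20-60% on change against about 80% on follow-up. It is higher when baselines are concentrated (60-68%) or when the risk of persisting pain rises with baseline (70-76%). If the effect is graded, change can beat unadjusted follow-up, but adjusting follow-up for baseline costs nothing against change and often gains. This should be corrected before outcomes are analysed.

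**What to change.** In Data analysis (Randomized clinical trial):

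- Make the primary analysis the Wong-Baker score at the primary follow-up timepoint.
- Compare the groups with baseline score as covariate (proportional-odds model or rank ANCOVA) or as stratum (van Elteren test).
- Report an effect estimate, such as the common odds ratio or the probability of a better score, with its 95% CI.
- Show change from baseline descriptively only.
- Do not substitute an unadjusted comparison of follow-up scores.

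Then reconcile this with Sample size and Outcomes, where the primary outcome is presence of pain: all three sections should name the same outcome, and the sample size should match the analysis chosen.

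The cost is a sentence or two of analysis wording plus that reconciliation. Baseline and follow-up scores are already to be collected, R is already named, and no extra visits or measurements are needed.
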